### Participants – eligibility criteria {10}

Individuals must be willing to attend the face-to-face rehabilitation programme to participate in the RCT element of this study. Participants who are not willing or able to attend will be offered the opportunity to partake in the qualitative semi-structured interviews (phase 2) of this study.

Participants are eligible if they are over the age of 18 years old, were NOT admitted to hospital during the acute phase of their Covid infection, have a clinician diagnosis of Long Covid (from a dedicated Long Covid assessment clinic), have ongoing symptoms that may be modifiable by a rehabilitation programme (such as breathlessness, fatigue, or reduced exercise tolerance), and are willing and able to provide informed consent.

Individuals will be excluded from the study if exercise is contraindicated as outlined in the American College of Sports Medicine guidance [23], further investigation/management for an unstable comorbidity is required, exercise-based rehabilitation has been attended/completed in the preceding 6 months, hospital admission was required during their most recent acute SARS-CoV-2 infection, they have severe debilitating fatigue (home bound or bed bound) that worsens with activity — regardless of formal post-exertional malaise/myalgic encephalomyelitis (ME) diagnosis, or they are not willing or unable to provide consent.

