Signs of post-exertional malaise and post-exertional symptom exacerbation will be monitored using the DePaul Symptom Questionnaire–Short Form (DSQ-SF) [25], modified Borg breathless scale [26], and Borg rate of perceived exertion (RPE) [27], and results were discussed by the healthcare professional with the participant at the start of each session. Adjustments to the exercise programme, or onward referral, will be made as necessary, and patients may be removed from the study if adverse events occur.

Clinical staff responsible for delivering the intervention have become experts in this now well-established intervention. Training will be provided to any new staff, and a competency scheme is in place to ensure there is standardisation of care.

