### Usual care (control) {6b}

Participants in the control arm will receive usual care for 6 weeks. Routine clinical care will continue, such as medical follow-up, mental health service provision, and other specialist services.

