### Criteria for discontinuing/modifying interventions {11b, 18b, 21b and 22}

Due to the nature of the trial, there are no formal stopping rules as no problems detrimental to the participant are anticipated (supported by data from the hospitalised trial [30]). The intervention will be discontinued if the participant withdraws consent or if a change in circumstance results in the participant becoming unsafe to engage in the intervention. Data collected up until the date of withdrawal will remain in the analysis with participants’ consent.

As the intervention is individualised, any modifications will be determined through discussions between the patient and healthcare professional. Reasonable adaptations to exercise will be made based on clinical judgement and participant need.

Participants will be carefully monitored with particular attention to those displaying signs of post-exertional malaise (PEM) and post-exertional symptom exacerbation (PESE) via the DePaul outcome measure. Steps have been taken to ensure those with known PEM/PESE are not recruited to this trial to ensure their symptoms are not worsened by rehabilitation. If it appears that someone is experiencing PEM/PESE during the intervention phase, then they will be suspended from the trial, upon discussion with the individual, and referred to the appropriate clinic(s).

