### Outcomes {12}

A comprehensive, individualised face-to-face assessment will be conducted for all participants, to include demographics of protected characteristics (to inform the secondary analysis of healthcare inequalities), social history (to include employment status, smoking history), history of presenting complaint (Long Covid history), and comorbidities. Participants’ home postcodes will be indexed to the indices of multiple deprivation (IMD) to inform socioeconomic status. All outcome measures will be performed before and after the 6-week intervention phase. The core outcome set for Long Covid [31] developed through international consensus was consulted to inform which outcome measures were selected for use in this study.

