#### Primary outcome

Maximal exercise capacity was measured by absolute change in ISWT distance (in metres) 6 weeks after baseline (±2 weeks). The ISWT will be performed in line with technical standards [32]. In brief, the test is an externally paced, incremental test that requires the patient to walk around a 10-m (m) course at a target speed dictated by audio bleeps. As a maximal, progressive test, the walking speed starts slowly but increases each minute, with the test terminated when the patient is no longer able to keep up with audio cues or by the assessor if the required speed is not attained. The test will be performed twice pre-intervention for familiarisation, with the highest distance achieved used for exercise prescription (ESWT speed). The test will be repeated once after the intervention (Table 1).

**Table 1 Tab1:** Secondary outcome measures

Acceptability	Physical Measures	Questionnaires
Quantitative measure of completion in the intervention group	Short physical performance battery (SPPB) [33]	Generic HRQoL: EQ-5D-5L [34]
Qualitative evidence via focus groups and semi-structured interviews	Physical activity monitoring: ActiGraph accelerometer device [35]	Fatigue: Functional Assessment of Chronic Illness Therapy Fatigue Scale (FACIT-Fatigue) [36]
	Maximum isometric quadriceps strength (kg) [37]	Depression: Patient Health Questionnaire (PHQ9) [38]
	Endurance Shuttle Walk Test (ESWT) (seconds) [39]	Anxiety: Generalised Anxiety Disorder 7-item scale (GAD7) [40]
		Breathlessness: MRC Dyspnoea scale [41]
		Covid-specific HRQoL: Modified C19-YRS [42]
		Cognitive Function: Montreal Cognitive Assessment (MoCA) [43]
		Post Exertional Malaise: DePaul Symptom Questionnaire Short Form (DSQ-SF) [25]

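### Suspending participants with post-exertional symptoms from the trial, not just from the exercise, would lose 6-week outcomes mainly in the rehabilitation arm and tilt the comparison towards rehabilitation

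*Protocol article*

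**What the plan says.** All references are to the protocol article.

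- *Criteria for discontinuing/modifying interventions*: if it appears that a participant is "experiencing PEM/PESE during the intervention phase, then they will be suspended from the trial", after discussion with that person, and referred on. Data collected before a withdrawal stay in the analysis if the participant agrees.
- *Face-to-face rehabilitation (intervention)*: the exercise programme can be adjusted or the patient referred on, and "patients may be removed from the study if adverse events occur". Post-exertional symptoms are monitored with the DSQ-SF and two Borg scales, and "results were discussed by the healthcare professional with the participant at the start of each session".
- *Usual care (control)*: "Participants in the control arm will receive usual care for 6 weeks". No trial symptom check between the two assessments is described for this arm.
- *Outcomes*: "All outcome measures will be performed before and after the 6-week intervention phase". The primary outcome is "absolute change in ISWT distance (in metres) 6 weeks after baseline". The DSQ-SF is also a listed secondary outcome, scheduled at enrolment and at 6–8 weeks.
- *Statistical analysis*: multiple imputation, described as permitting a full ITT analysis, is one of two sensitivity analyses of the primary outcome.
- *Oversight and monitoring*: adverse events in either group are recorded and reported.
- On eligibility, *Criteria for discontinuing/modifying interventions* says "Steps have been taken to ensure those with known PEM/PESE are not recruited to this trial". The related exclusion in *Participants – eligibility criteria* applies where "they have severe debilitating fatigue (home bound or bed bound) that worsens with activity".

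**The concern.** Whether someone should stop exercising is a clinical matter and is not judged here. Whether that person's outcome is still measured is a design matter, and the two sections quoted make the second follow from the first. If participants leave because they respond badly to the exercise, and leave mainly from one arm, those who remain are no longer the randomised groups. The retained rehabilitation participants are then a selected set who tolerated the programme, compared with an almost unselected control arm.

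Two comparisons are exposed. One is ISWT change, if the main test uses observed values. The other is the DSQ-SF, which both triggers suspension and serves as an endpoint: intervention participants with marked post-exertional symptoms could leave before the 6-week score, while controls with similar symptoms would stay in. The fatigue and quality-of-life questionnaires would lose the same people.

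**Working it through.** **Does the wording cost outcome data?**

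1. Both sections distinguish changing the intervention from leaving the trial. One lists programme adjustments before it mentions removal. The other speaks separately of discontinuing the intervention. The terms suspended from the trial and removed from the study therefore cannot be assumed to mean only stopping sessions.
2. Outcomes exist at two time points only. For someone suspended mid-programme, keeping data up to withdrawal preserves the baseline and any session-level symptom scores, but no 6-week outcome.
3. No sentence says that suspended or removed participants return, or that they are still invited to the 6-week assessment.
4. The repeated checks take place at sessions, and only the rehabilitation arm has sessions.
5. Because the imputed ITT analysis is labelled a sensitivity analysis, the main t-test is presumably run on observed values.

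**How large could the effect be?**

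The plan gives no figure on this point, so there is none to reproduce. Inputs:

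- Arm size: 56 randomised 1:1, so 56/2 = 28 (*Sample size*, *Randomisation*).
- Target difference 50 m and SD 17 m (*Sample size*).
- Number removed, k, and shortfall in mean ISWT change of those removed against those retained, L: not in the documents, assumed.

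With m the mean change in those retained, the full-arm mean is [k(m − L) + (28 − k)m]/28 = m − kL/28. Analysing only those retained therefore overstates the arm mean by

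bias = k × L / 28.

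| k | L (m) | Bias (m) | Share of 50 m |
|---|---|---|---|
| 2 | 17 | 2×17/28 = 1.2 | 2% |
| 5 | 17 | 5×17/28 = 3.0 | 6% |
| 2 | 50 | 2×50/28 = 3.6 | 7% |
| 3 | 100 | 3×100/28 = 10.7 | 21% |
| 5 | 100 | 5×100/28 = 17.9 | 36% |

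**Effect on false-positive rate.** A simulation (20,000 runs, 28 per arm, two-sided t-test at 5%) set the true effect over all randomised participants to zero. Affected participants change by −50 m on average and the rest by +50f/(1 − f), where f is the fraction affected and removed. The SD was taken as 51 m, because a two-sided two-sample t-test with 50 m and 90% power reaches the plan's 23 per group at about that SD. The stated 17 m gives 4 per group, which is a separate matter.

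| f | Expected spurious gain (m) | Simulated (m) | Rejection rate |
|---|---|---|---|
| 5% | 2.6 | 2.8 | 5.4% |
| 10% | 5.6 | 5.5 | 6.5% |
| 20% | 12.5 | 12.3 | 13.5% |

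**The case against.** The strongest reply is that the loss of outcomes is inferred. The suspension rule sits in a section about discontinuing the intervention, follows a discussion with the individual, and may be temporary. Removal for adverse events is only a possibility. The general rule is that all outcomes are measured before and after. Completion is defined as 75% attendance or attending follow-up, so follow-up of people with poor attendance is foreseen, and a full ITT analysis is planned. All this shows that the intention may be sound. It does not remove the difficulty, because staff who follow the two sentences literally would end participation and nothing in the article tells them otherwise.

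Four stronger readings are tempting and are not supported:

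- *That only the intervention arm can lose people.* The rule is not worded by arm, and adverse events are logged in both. The text supports mainly, because the repeated checks are described for one arm only.
- *That harm would be hidden.* Adverse events are recorded, reported and classified for relatedness in both groups, session symptom scores exist, and people who drop out are sought for interview. What is at risk is the 6-week outcome scores.
- *That imputation must fill the gaps from people who tolerated exercise.* Standard multiple imputation under missing at random would tend to do so, but the imputation model is not stated, and the article may leave it to an analysis plan.
- *That the eligibility statements flatly contradict each other, so events are likely.* The steps said to have been taken may be the multidisciplinary review and clinician referral described under *Trial design and setting* and *Recruitment*. The listed exclusion does not by itself cover ambulatory people with known PEM/PESE, which leaves a point to reconcile but gives no event rate.

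It is also fair to say that the magnitude rests on assumptions, and that shortfalls of 50 to 100 m are 3 to 6 times the stated SD of 17 m.

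**Conclusion.** The concern holds as a flaw in the wording of the plan. As written, it merges stopping the exercise with leaving the trial, and so would lose 6-week data mainly in the intervention arm and mainly for poor responders. The direction favours rehabilitation whenever those lost do worse than those retained.

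The size cannot be known from the documents. For 2 to 5 people lost of 28, it runs from about 1–3 m (17 m shortfall) to 4–18 m (50–100 m shortfall), all assumed. If such losses are few the ISWT bias is small, and the simulated rejection rate stays near 5% when 5% of the arm is lost. The DSQ-SF comparison is affected more directly, because the same instrument drives the suspension; that effect was not quantified. The conclusion also assumes that the main test uses observed values, as the labelling of the sensitivity analyses implies. The change is worth making because an outcome that was never collected cannot be recovered at analysis.

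**What to change.** 1. Reword *Criteria for discontinuing/modifying interventions* and *Face-to-face rehabilitation (intervention)* so that the clinical decision about exercise sessions is separate from trial participation. The clinical decision itself stays with the treating team.
2. State that, unless consent is withdrawn, these participants remain in follow-up, are invited to the scheduled 6-week assessment (questionnaires including the DSQ-SF, and physical tests where the clinician judges them safe), and are analysed as randomised.
3. Some ISWT values will still be missing, because physical testing may not be appropriate for everyone affected. A sensitivity analysis that assumes poorer outcomes for suspended participants (delta-adjusted imputation) would be a useful addition, as would a count of suspensions and removals by arm. Both can go in the analysis plan.
4. Reconcile the eligibility criteria with the statement that people with known PEM/PESE are not recruited, so that it is clear whether ambulatory people with known PEM/PESE are eligible.

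The cost is a minor amendment, with matching participant information wording if it repeats the present text, and a few follow-up visits with people who have stopped sessions. The 6-week visit is already in the schedule.

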### Provisions for post-trial care {30}

After involvement in the trial has concluded, individuals allocated to the control group will be offered face-to-face rehabilitation if desired.

### Outcomes {12}

A comprehensive, individualised face-to-face assessment will be conducted for all participants, to include demographics of protected characteristics (to inform the secondary analysis of healthcare inequalities), social history (to include employment status, smoking history), history of presenting complaint (Long Covid history), and comorbidities. Participants’ home postcodes will be indexed to the indices of multiple deprivation (IMD) to inform socioeconomic status. All outcome measures will be performed before and after the 6-week intervention phase. The core outcome set for Long Covid [31] developed through international consensus was consulted to inform which outcome measures were selected for use in this study.

#### Primary outcome

Maximal exercise capacity was measured by absolute change in ISWT distance (in metres) 6 weeks after baseline (±2 weeks). The ISWT will be performed in line with technical standards [32]. In brief, the test is an externally paced, incremental test that requires the patient to walk around a 10-m (m) course at a target speed dictated by audio bleeps. As a maximal, progressive test, the walking speed starts slowly but increases each minute, with the test terminated when the patient is no longer able to keep up with audio cues or by the assessor if the required speed is not attained. The test will be performed twice pre-intervention for familiarisation, with the highest distance achieved used for exercise prescription (ESWT speed). The test will be repeated once after the intervention (Table 1).

**Table 1 Tab1:** Secondary outcome measures

Acceptability	Physical Measures	Questionnaires
Quantitative measure of completion in the intervention group	Short physical performance battery (SPPB) [33]	Generic HRQoL: EQ-5D-5L [34]
Qualitative evidence via focus groups and semi-structured interviews	Physical activity monitoring: ActiGraph accelerometer device [35]	Fatigue: Functional Assessment of Chronic Illness Therapy Fatigue Scale (FACIT-Fatigue) [36]
	Maximum isometric quadriceps strength (kg) [37]	Depression: Patient Health Questionnaire (PHQ9) [38]
	Endurance Shuttle Walk Test (ESWT) (seconds) [39]	Anxiety: Generalised Anxiety Disorder 7-item scale (GAD7) [40]
		Breathlessness: MRC Dyspnoea scale [41]
		Covid-specific HRQoL: Modified C19-YRS [42]
		Cognitive Function: Montreal Cognitive Assessment (MoCA) [43]
		Post Exertional Malaise: DePaul Symptom Questionnaire Short Form (DSQ-SF) [25]

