### Face-to-face rehabilitation (intervention) {11a and 11c}

Individuals will complete an individualised symptom-titrated programme of exercise, education, and self-management for 6 weeks. The programme will comprise two supervised sessions per week delivered by healthcare professionals.

Six weeks have been purposefully selected as the intervention period to align with current clinical provision in Leicester. Aligning the intervention period with that used clinically will consolidate clinical expertise and support implementation.

The rehabilitation programme will consist of aerobic exercise (i.e. treadmill/ground walking at 80% of the incremental shuttle walk test (ISWT) speed where tolerated and lower-limb cycling on a static bike) and resistance exercise training (upper and lower limb strength exercises). The exercise intensity and duration will be tailored to the individual’s current abilities, assessed in their first visit.

In addition to the supervised sessions, patients will be asked to perform home-based exercise sessions which align with the supervised sessions to include the following: daily walking, three aerobic exercise sessions, and one resistance exercise session each week. Participants will be asked to record their progress in a self-reported diary, which will be used in conjunction with self-reported symptoms at the face-to-face sessions for the delivering clinicians to monitor symptoms and guide exercise modifications and progression.

Each rehabilitation session will include an educational discussion (approx. 30–60 min) delivered by a member of the multidisciplinary team. These discussions will be facilitated by information sheets saved from the Your COVID Recovery (YCR) website repository. Topics covered will include the following: getting moving again, managing activities of daily living, breathlessness, fatigue management, and recognising symptoms of worsening in response to exercise, fear and anxiety, mood and coping, memory and concentration, cough, eating well, sleep hygiene, goal setting, headaches, managing symptom exacerbation and fluctuations, and returning to work. At the end of each session, there will be an opportunity for discussion and question and answer.

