**ASSESSMENTS:**			
Incremental Shuttle Walking Test (ISWT)	X		X
Short Physical Performance Battery (SPPB)	X		X
Quadriceps Strength	X		X
Physical Activity Monitoring	X		X
Endurance Shuttle Walking Test (ESWT)	X		X
EuroQol 5-Dimension 5-Level (EQ-5D-5L)	X		X
Covid-19 Yorkshire Rehabilitation Scale (C19-YRS)	X		X
Patient Health Questionnaire-9 (PHQ-9)	X		X
Generalised Anxiety Disorder-7 (GAD-7)	X		X
Medical Research Council (MRC) Dyspnoea Scale	X		X
Functional Assessment of Chronic Illness Therapy – Fatigue (FACIT-F)	X		X
Montreal Cognitive Assessment (MOCA)	X		X
DePaul Symptom Questionnaire – Short Form (DSQ-SF)	X		X

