### Uptake, compliance and completion

There will be a screening log recorded of the number of people approached, which will be used to compare with those who uptake and consent.

Quantitative measure of completion in the intervention group will be defined as the number of patients attending 75% of their scheduled sessions (75% selected to align with national rehabilitation guidance [44]) or attended follow-up assessment.

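### The primary outcome definition opens the follow-up ISWT window at week 4, two weeks before the schedule does and before the 6-week programme ends

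*Protocol article*

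**What the plan says.** The protocol article gives the timing of the follow-up ISWT in four places.

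- **Primary outcome, definition.** The endpoint is "absolute change in ISWT distance (in metres) 6 weeks after baseline (±2 weeks", a symmetric tolerance counted from baseline.
- **Primary outcome, test procedure.** Later in the same paragraph: "The test will be repeated once after the intervention".
- **Outcomes {12}, opening paragraph.** "All outcome measures will be performed before and after the 6-week intervention phase". This covers every outcome and both arms.
- **Table 2 (SPIRIT figure).** The time points are 0 for enrolment, 0–6 weeks for the intervention and 6–8 weeks for post-allocation. The row that begins "Incremental Shuttle Walking Test (ISWT" is marked only under enrolment and post-allocation. The rehabilitation and control rows are both marked under 0–6 weeks.

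The intervention section describes an "individualised symptom-titrated programme of exercise, education, and self-management for 6 weeks" and adds: "The programme will comprise two supervised sessions per week delivered by healthcare professionals". The Usual care section gives the control arm a period of 6 weeks as well.

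**The concern.** The window sits inside the definition of the primary endpoint, so site staff and the analyst will use it to decide whether a test counts. Its early half does not fit the rest of the article. An intervention participant tested at week 4 or 5 has not finished a 6-week programme, yet the definition accepts the result as the primary outcome.

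Two consequences are possible, and they pull in opposite directions.

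- **Early tests in the intervention arm** measure an incomplete course and would tend to dilute the estimated effect.
- **Early tests mainly in the control arm** would give controls less time to recover than intervention participants, which would tend to favour rehabilitation. The Background says that earlier, mostly observational studies could not separate natural recovery from the benefit of rehabilitation. A randomised comparison separates them only if elapsed time to the test is comparable between arms.

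**Working it through.** **Inputs**

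- Text window: 6 weeks ± 2 weeks from baseline (Primary outcome).
- Schedule window: 6 to 8 weeks (Table 2, post-allocation column).
- Programme: 6 weeks, 2 supervised sessions per week (Face-to-face rehabilitation section).
- Completion threshold, for context: "the number of patients attending 75% of their scheduled sessions" (Uptake, compliance and completion; attending follow-up is given there as an alternative).

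**Step 1. The two windows**

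| Source | Earliest | Latest |
|---|---|---|
| Primary outcome definition | 6 − 2 = week 4 | 6 + 2 = week 8 |
| Table 2 | week 6 | week 8 |
| Difference | 2 weeks | 0 |

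The overlap is weeks 6 to 8, and any test in that range satisfies both. The conflict is confined to week 4 up to just under week 6. A test at week 5 is in window under the definition and out of window under Table 2.

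**Step 2. How much of the programme can precede an early test**

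Full programme: 2 × 6 = 12 supervised sessions. If the programme starts at baseline:

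- by week 4, at most 2 × 4 = 8 sessions, and 8/12 = 67%;
- by week 5, at most 2 × 5 = 10 sessions, and 10/12 = 83%.

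The 75% threshold applied to 12 sessions is 0.75 × 12 = 9. At week 4 even perfect attendance falls one session short of it.

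**Step 3. A delayed start**

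The window is counted from baseline, not from the first session, and the article does not give the gap between them. Call it g weeks. Sessions possible by week 4 are then 2 × (4 − g), and the programme ends at week 6 + g. As an illustration only, g = 1 gives 2 × 3 = 6 of 12 sessions (50%) by week 4 and a programme end at week 7. With any delay, a visit at exactly week 6 could also come before the last session. For this reason the corrected wording needs the condition that the test follows the intervention period as well as the calendar window.

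**Step 4. Largest difference in elapsed time between two in-window participants**

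- Text window: 8 − 4 = 4 weeks.
- Table 2 window: 8 − 6 = 2 weeks.

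If controls were tested at week 4 and intervention participants at weeks 6 to 8, the difference in recovery time would be 6 − 4 = 2 to 8 − 4 = 4 weeks. This describes what the wording admits, not what is planned. Aligning the window halves the maximum but does not remove it, so control visits also need to be booked to matching elapsed times.

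**The case against.** The strongest reply is that the article already settles the matter. The same paragraph says the test comes after the intervention, the opening of Outcomes {12} says so for all measures, and Table 2 has no ISWT mark during weeks 0 to 6. Read together, the operative window is weeks 6 to 8, and a week-4 test would breach three other statements. Most of this stands: the early half of the window is probably unintended, and the two rules are not mutually exclusive, because a visit at weeks 6 to 8 meets both. It does not remove the defect. The endpoint definition still states a lower limit that the rest of the article contradicts, and it is the more permissive of the two.

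Two stronger readings are tempting and should be resisted.

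- **A reader might infer that only the loose window governs when controls are tested, and hence that the plan builds in bias between the arms.** The article does not support this. The Usual care section gives controls a 6-week period, Table 2 marks the control row under weeks 0 to 6 with one follow-up column for both arms, and the rule in Outcomes {12} applies to everyone. Nothing indicates that controls would be seen earlier.
- **A reader might convert the 67% of sessions into a loss of power.** That would need gain to accrue linearly, every participant to be tested at week 4, and a standard deviation well above the 17 m in the Sample size section. None of the three is in the article. With the stated 17 m the loss would be negligible. Whether 17 m is itself sound is a separate question and should not be brought in here.

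**Conclusion.** The point stands as an internal contradiction in the primary endpoint's timing. The definition admits tests from week 4; Table 2 and two sentences in the text require week 6 or later. The disputed interval is two weeks, and at its start at most 8 of 12 sessions (67%) can have taken place. The session count assumes that the programme starts at baseline; a later start lowers it.

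The effect on the result cannot be sized from the article. Its direction depends on which arm is tested early, and no planned or actual visit times are given. The sample size is unaffected. Both windows are stated, so this is not detail left to a longer protocol or an analysis plan. It should be corrected because it concerns the primary outcome and costs almost nothing, but it is not a fatal flaw.

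**What to change.** In the Primary outcome section, replace the ±2-week tolerance with the Table 2 window: 6 weeks after baseline, −0/+2 weeks (weeks 6 to 8), and after the end of the intervention period. State that the window is identical in both arms. Add an instruction that control visits are booked to the same elapsed time from baseline as intervention visits. Report time from baseline to the follow-up ISWT by arm, so that readers can see whether timing was balanced.

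The cost is a text amendment, a scheduling instruction, one descriptive line in the results and slightly less booking flexibility. The Trial status section says recruitment began in November 2024, so the wording should be settled before the data are analysed.
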